
### Data collection

Screening of patients at the study wards will be performed by the researchers, who are employed by the hospital. This will be done using information from the EHR and, if any unclarities occur, through contact with the ward HCPs. The researchers will invite eligible patients to participate, and patients willing to participate will be asked to sign informed consent (online supplemental material I). Data will be collected from all participants, regardless of their adherence to the intervention, provided they do not withdraw their consent to participate in the study. This approach ensures complete follow-up data for inclusion in the intention-to-treat (ITT) analysis. The data collection will proceed in several steps (table 1) and will be conducted by researchers in the research team and trained research assistants. To ensure uniformity of data collection, standard operating procedures have been developed. Data will be pseudonymised and transferred to case report forms (CRFs) in an electronic data capture system, Research Electronic Data Capture (REDCap).^51^ All data processing and analysis will be based on the data in these CRFs and will be shared and discussed in pseudonymised form. Any forms and electronic files that reveal research data of an individual patient will be stored in a locked archive at the hospital pharmacy. Access to the final trial data set will be restricted to the members of the research team.

#### Demographic data

Demographic data collected from the EHR will include age, gender, renal function, admission and discharge dates, medication treatment at admission and discharge, whether the patient has support by automatic dose-dispensation of medications, disease diagnoses, primary diagnosis for admission, home care support, whether the patient lives alone and the number of emergency department visits and hospital admissions in the past year. Information about patients’ education level will be gathered through the researchers asking the patients at inclusion.

#### Completeness and quality of discharge documentation

After patient discharge, the discharge letter, discharge summary and referrals to next healthcare providers for follow-up will be extracted from the EHR for scoring according to CMDD-M (online supplemental material III). The instrument was specifically developed to be used in clinical settings in Sweden. Initial validation demonstrated that the instrument is feasible for use in our setting.^45^ Inter-rater reliability was assessed using Cohen’s weighted kappa with both linear (Kw linear) and quadratic (Kw quadratic) weights. The Kw linear for the comparison between two clinical pharmacists was 0.92, while the comparison between their consensus and a geriatrician yielded a Kw linear of 0.64. Similarly, the Kw quadratic was 0.97 for the comparison between the pharmacists and 0.80 for the comparison between their consensus and the geriatrician. These findings indicate moderate to almost perfect reliability between raters and suggest that the CMDD-M instrument provides robust reliability in assessing the quality and completeness of medication-related discharge documentation in older hospitalised patients.^45^ The CMDD-M was selected as the primary outcome, as it was deemed the most appropriate and feasible option. Although only component 2 (preparation of medication-related discharge documentation) of the intervention is expected to have a direct effect on this measure, components 1 (information package provided to patients) and 3 (facilitation of discharge communication) are also expected to exert indirect effects on the CMDD-M score by encouraging patients/informal caregivers to request the discharge documents to which they are entitled and to ask more questions about their medications. This, in turn, is anticipated to prompt physicians to provide more explicit information in the documentation. Several alternative outcomes were considered but found to be less suitable, for example, unplanned hospital revisits would require an unfeasibly large sample size; the PIMCH-Q lacks complete validation; and measuring adherence to medication changes raised concerns about precision. These outcomes were therefore designated as secondary. Given its design and focus on aspects directly relevant to our intervention, we anticipate it to effectively capture meaningful changes within our study sample, even though the responsiveness of the CMDD-M to changes in the completeness and quality of discharge documentation in response to an intervention has not yet been evaluated. To ensure objectivity, the assessment using the CMDD-M will be conducted by the researchers in a blinded manner. Data extracted from the EHR will be masked to prevent assessors from linking patients to specific time periods, ensuring they remain unaware whether the patient belongs to the control or intervention group.

#### Patients’ experience

The PIMCH-Q will be sent to patients by mail or email, depending on their preferences, 1 week after the discharge date (online supplemental material IV). The patients are asked to answer the questionnaire as soon as possible. If no response is received within 10 days, the research team will follow up with a reminder via email or phone. During the reminder call, patients will also be offered the option to respond by phone if preferred. The PIMCH-Q was selected for this study because, to the best of our knowledge, no existing instrument adequately captures medication-related patient experiences during hospital discharge. While its responsiveness has not yet been validated, the tool was specifically designed to assess patient involvement in medication communication and confidence in medication management post-discharge, which are core aspects of this study. Despite the need for further validation, the PIMCH-Q remains the most suitable tool for achieving our study objectives.

#### Adherence to medication changes

Data about the lasting medication changes made and prescribed during hospitalisation will be gathered from the EHR. Information on medications dispensed from pharmacies for each patient 120 days post-discharge will be obtained from the Swedish National Board of Health and Welfare’s national prescribed drug register. This register contains data on all medications dispensed from community pharmacies in Sweden on a patient level. The extracted data will include the medication name, the anatomical therapeutic chemical code, strength, prescribed quantity, collected quantity, prescription date, collection date, prescriber’s profession and workplace. The assessment of the number of instances of non-adherence will be conducted by the researchers.

#### Healthcare utilisation

Unplanned hospital revisits, readmissions, emergency department visits and time to these hospital revisits within 90 days will be extracted from the EHR. The assessment of whether the hospital readmissions were potentially medication-related will be conducted retrospectively and blinded, using the AT-HARM10 tool^49^ through information from the EHR. The assessment will be conducted by one clinical pharmacist and one physician who are not otherwise involved in the study. Initially, they will independently evaluate each case, followed by a discussion to reach consensus on cases where their initial assessment (eg, whether a readmission is potentially medication-related) differed.

### Process evaluation

A mixed-method approach, combining both quantitative and qualitative methods, will be used for a process evaluation to assess adherence to the study protocol and explore the implementation of the intervention. The evaluation will be guided by the framework for process evaluation developed by the United Kingdom Medical Research Council.^52^

#### Quantitative process evaluation

The quantitative process evaluation will include all patients in the study to gain insight into the extent of intervention implementation, the degree to which some intervention components may already be in place during the control period and adherence to the study protocol. The following data will be collected from the EHR:

The proportion of control and intervention patients who received a discharge letter.The proportion of control and intervention patients for whom the clinical pharmacist prepared medication discharge documentation.The proportion of intervention patients who received the information package.The proportion of control and intervention patients for whom the physician used the medication discharge documentation prepared by the pharmacist. This is measured by manually comparing the content of the prepared medication discharge documentation by the pharmacist with the actual medication summary in the discharge letter and final note written by the physician.The proportion of intervention patients who are reminded by the pharmacist to review the information package.The proportion of intervention patients who wish to have an informal caregiver present at the discharge consultation, and the proportion of those cases where the pharmacists contacts the informal caregiver to be present.The proportion of intervention patients who wish to have a follow-up call with a pharmacist after discharge, received the follow-up call and whether it led to any pharmacist intervention, including details of the intervention.

Additional data collection methods:

The proportion of all employed physicians and clinical pharmacists at the study wards who attend the training sessions. All HCPs attending the training sessions will be registered by the researchers. Data on HCPs who complete digital training sessions will be extracted from the digital training platform.The response rate of PIMCH-Q, along with the distribution method (paper, telephone or digital). This will be extracted from REDCap.The proportion of control and intervention patients who recall having a discharge consultation, whether they wished to have an informal caregiver present, whether an informal caregiver was actually present, their desire for a follow-up call and whether they received one. For control patients, these questions aim to determine the extent to which intervention components are performed as part of standard care. Additionally, for intervention patients, the proportion of patients who recall receiving the information package (intervention component 1) and their perception of it will be asked. These questions will be sent to patients alongside the PIMCH-Q.The amount of time used by pharmacists to deliver each component of the intervention, as well as the overall intervention, will be measured in a subset of the sample.

#### Qualitative process evaluation

Regular meetings with the pharmacists delivering the intervention will be scheduled during the intervention period to discuss and address implementation barriers that could be resolved to support successful implementation.

At the conclusion of the intervention phase, a qualitative process evaluation will be conducted with HCPs and patients. This will involve semi-structured interviews and focus groups with HCPs, specifically physicians and pharmacists from the study wards, who were actively involved in delivering the intervention, to explore their experiences and perceptions of its implementation. Semi-structured interviews will also be conducted with patients, and when applicable their informal caregiver, who received components of the intervention. This qualitative component will offer insights into how patients perceived the intervention. Patient interviews will be conducted either shortly before or within 1 week after discharge. A purposeful sampling approach will be adopted to obtain maximum variation. For HCP focus groups and interviews, variation will be sought in terms of sex, working experience and study ward.^53^ The same approach will be applied for patient interviews, but this time to capture heterogeneity in age, sex and health complexity. The concept of information power will guide the decision of sample size.^54^ All interviews and focus groups will be audio-recorded and transcribed verbatim. The data will be analysed thematically.^55^

### Sample size calculation

The sample size calculation is based on the primary outcome, which is the quality of medication-related discharge documentation measured using the CMDD-M. The intervention will be deemed successful if the average score is significantly higher in the intervention group compared with the control group. For the calculation, we assumed an evenly distributed sample between the two groups and set the target difference in CMDD-M scores at 1 point. This conservative target was chosen as it represents the smallest measurable step in the instrument. In practice, a 1-point difference may indicate the inclusion of medication changes in the discharge letter or discharge summary. Such an improvement reflects a critical enhancement in quality, with important implications for patient safety and continuity of care. Data from the pilot studies indicated that the baseline value for CMDD-M was 3.9 (SD 2.6) ([name], [name], [name], [name], *et al*: Facilitating patient empowerment at hospital discharge: A pilot study testing the feasibility of the IMPACT-care intervention, unpublished). Due to the maximum score limit in CMDD-M, the variance in scores is expected to differ between the control and intervention periods. This difference arises as scores may cluster near the upper limit, particularly in the intervention period where improved performance is anticipated, potentially leading to reduced variability compared with the control period. A two-sided t-test with Welch’s correction for df (to account for the variance difference between groups) was used. A power of 0.8 was considered sufficient to detect an increase, with a 5% two-sided significance level. Based on these assumptions, a sample size of 115 patients per group, for a total of 230 patients, is required.

Additionally, a permutation test using the Mann-Whitney U test was performed to assess the robustness of the t-test, yielding similar results.

### Statistical analysis

A full statistical analysis plan will be finalised prior to any analyses. Statisticians from the Uppsala Clinical Research Center will oversee the statistical analyses. The primary analysis will follow the ITT principle, including all included patients in their assigned groups, regardless of protocol adherence. Additional analyses will include per-protocol analyses, that is, excluding patients with protocol violations.

Descriptive analyses of the study population will be performed, with continuous data presented as mean±SD for normally distributed variables or as median and range for non-normally distributed variables. Categorical variables will be reported as frequencies and percentages. All outcomes will be summarised by study group, overall and by ward, descriptively. Comparative statistics between study groups will be conducted, with all statistical tests being two-sided and a p value<0.05 considered statistically significant.

Models for analysing primary and secondary outcomes will include both unadjusted and fully adjusted analyses. Adjustments will account for age, gender, education level, ward type (geriatric or surgical), number of medication changes persisting post-discharge, number of medications at discharge, support by automatic dose-dispensation of medications and duration of hospitalisation. Effect estimates, including ORs, HRs and rate ratios will be presented with 95% CI and p values.

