#### Component 2: Preparation of medication-related discharge documentation

Incompleteness and poor quality of medication-related discharge communication from hospitals is a common problem,^40 41^ making it difficult for subsequent HCPs to trust this information.^12 17 42^ Pharmacist involvement can significantly improve the completeness and quality of such communication.^40 41^ Consequently, in our study, the pharmacist will review relevant parts of the patient’s EHR and medication list prior to discharge to identify any lasting medication changes made during the hospitalisation. The pharmacist will collaborate with the discharging physician to reconcile follow-up plans for these changes. All medication changes, including reasons for the adjustments (when known), planned treatment duration, follow-up plans and the ward’s phone number for any post-discharge inquiries from the patient, will be documented in a standardised manner in the EHR by the pharmacist. This documentation will form the basis for detailing medication changes and follow-up plans in the patient’s discharge letter and the discharge summary intended for the next healthcare provider, both of which are written by a ward physician.

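### The adjusted models mix pre-intervention covariates with three variables settled only at discharge, and leave out past-year hospital use and admission medications, which the trial already collects

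*Protocol article*

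**What the plan says.** The protocol's Statistical analysis section states: "Models for analysing primary and secondary outcomes will include both unadjusted and fully adjusted analyses". One covariate list serves all of them. It opens with age, gender, education level and ward type and ends with "number of medication changes persisting post-discharge, number of medications at discharge, support by automatic dose-dispensation of medications and duration of hospitalisation".

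Four other parts of the protocol bear on this list:

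- **When the intervention acts.** Under Component 1 the booklet and a consultation are given at admission to the study ward. Under Component 2 the pharmacist works before discharge to "identify any lasting medication changes made during the hospitalisation", agrees follow-up plans with the physician, and enters all changes in the health record in a standard form.
- **Where the change count comes from.** The data collection section on adherence takes lasting changes from the same health record. The control period section says that pharmacists help with discharge documents only now and then, and not in a standard way.
- **What else is collected.** The Demographic data section lists medication at admission, renal function, diagnoses, home care, living alone and "the number of emergency department visits and hospital admissions in the past year". None of these is in the adjustment set.
- **Timing of baseline data.** Table 1 marks demographic data at both admission and discharge. No time point is given for dose-dispensation support.

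**The concern.** The two groups are enrolled in successive periods without randomisation. The adjusted estimate is therefore the one a reader will use to judge whether case mix explains the difference. For that purpose covariates should be fixed before the intervention can act and should capture how the two intakes differ.

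The list departs from this in two ways. First, three of its members are settled after the intervention has started. If the intervention changes one of them, adjustment takes that pathway out of the estimate. If the intervention only causes changes to be recorded more fully, the covariate is measured differently in the two groups. In both cases the adjusted coefficient is no longer the total effect of the intervention.

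Second, the list holds the medication count at discharge but not at admission, and it omits past-year hospital use. Past use is a natural predictor of unplanned revisits, readmissions and emergency department visits. If it differs between periods, those models carry the difference as if it were an effect.

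**Working it through.** **The plan's own figure, for scale.** The authors "set the target difference in CMDD-M scores at 1 point", with SD 2.6 from the pilot, power 0.8 and two-sided 5%. With equal SDs the normal formula gives 2 × (1.960 + 0.842)² × 2.6² / 1² = 106.1, so 107 per group, and an exact Welch calculation gives 108. The stated 115 is not reproduced from these inputs, but it errs on the safe side: at SD 2.6 it has about 82.8% power. This neither supports nor weakens the present point. It only gives the scale for the power figures below.

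**Which covariates can the intervention reach?**

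- Age, gender, education and ward type: no.
- Number of lasting changes: possibly, through pharmacist review or through fuller recording in the source record.
- Number of medications at discharge: possibly, through the same review.
- Length of stay: settled only at discharge; the documents describe no specific route.
- Dose-dispensation support: unclear, since no time point is stated. It is not counted here as a discharge-time variable.

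**Size of the shift from a discharge-time covariate.** Let the true total effect be 1.0 point, let the intervention move the covariate by g SD, and let the covariate move CMDD-M by b points per SD. The adjusted coefficient is then 1 − g × b. The algebra is the same if g is only a shift in recording: replacing the true value M by M + g for intervention patients moves −g × b into the group coefficient. The documents give neither g nor b, so all values are assumptions. Power is for 115 per group with SD 2.6 in both groups.

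| g | b (absolute value) | b positive: estimate, power | b negative: estimate, power |
|---|---|---|---|
| 0 | any | 1.00, 83% | 1.00, 83% |
| 0.1 | 0.3 | 0.97, 80% | 1.03, 85% |
| 0.3 | 0.5 | 0.85, 69% | 1.15, 92% |
| 0.5 | 0.8 | 0.60, 41% | 1.40, 98% |

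A simulation of the row g = 0.3 with b = +0.5 gave 1.00 unadjusted and 0.85 adjusted.

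In natural units, assume that the intervention adds 0.5 to 1.0 recorded changes per patient and that each change lowers CMDD-M by 0.1 to 0.4 points. The shift is 0.5 × 0.1 = 0.05 to 1.0 × 0.4 = 0.40, so the adjusted estimate would be inflated to between 1.05 and 1.40.

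**Size of an omitted covariate in the revisit models.** Assume no true effect, a prior-year admission in 45% of controls and 35% of intervention patients, a 30% revisit risk without one, and an OR of 2.25 for prior admission.

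- Risk with prior admission: odds 0.30/0.70 × 2.25 = 0.964, so risk 0.491.
- Controls: 0.45 × 0.491 + 0.55 × 0.30 = 0.386.
- Intervention: 0.35 × 0.491 + 0.65 × 0.30 = 0.367.
- Spurious OR: (0.367/0.633) / (0.386/0.614) = 0.92.

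The 10-point imbalance is an illustration. The documents report none.

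**The case against.** The strongest reply is that these variables are mainly case mix. Component 2 has the pharmacist find changes that have already been made. The control period section leaves changes to the medication list to physicians and nurse practitioners, and pharmacists already assist with medication reviews in usual care. Data collection follows standard procedures. On that reading the number of changes measures how much there is to document, and dropping it could leave confounding behind.

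Much of this stands. A reader might infer that the adjusted effect is biased, but no part of the protocol shows that the intervention alters prescribing, medication counts or length of stay. Only a possible bias is supported. Usual-care reviews do not, however, remove the difference in how changes are recorded in the two periods.

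It is also fair that nothing shows past-year use to differ between periods, since the wards and criteria are the same, and that no link from past-year use to CMDD-M is given. The omission therefore weighs mainly on the secondary hospital-use outcomes.

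Finally, the number of changes is the number of chances to be non-adherent. Removing it from every model would be wrong for the adherence outcomes.

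A reader might also infer that two unranked models give two chances of success, because the success rule says: "The intervention will be deemed successful if the average score is significantly higher in the intervention group compared with the control group". The documents do not say that either result may count. They defer to a full analysis plan that is not shown, and naming the deciding model is commonly left to it. That question is not part of this point.

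**Conclusion.** The point holds in a limited form. The protocol itself fixes an adjustment set that includes three discharge-time variables which the intervention or its recording could affect, and it leaves out pre-admission variables that the trial collects. The adjusted estimate may therefore not be the total effect.

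The error could go either way. The range of 0.60 to 1.40 for a true 1-point effect, and the spurious OR of 0.92 for revisits, rest wholly on assumed inputs; with no shift and no imbalance both vanish. The unadjusted analyses are free of the first problem but do nothing about case mix.

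This is a worthwhile and inexpensive improvement to make before analysis. It is not a demonstrated bias, and it does not invalidate the study.

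**What to change.** Specify the main adjusted model with covariates fixed before the intervention: age, gender, education, ward, number of medications at admission, dose-dispensation support as it stood before admission, and past-year emergency department visits and hospital admissions. Use this set for the primary and secondary outcomes.

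Report the current set, with the number of lasting changes, medications at discharge and length of stay, as a labelled sensitivity analysis.

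Make one exception. Keep the number of lasting changes in the adherence analyses, as an offset (log count) in the quasi-Poisson model and as a covariate in the logistic model for full adherence. Box 1 excludes patients with no lasting change, so the log is always defined. The possibility of unequal recording between periods remains there and should be stated.

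The cost is wording in the analysis plan plus a check that dose-dispensation support is recorded as of admission. No new variable is needed. The price is some loss of precision and possibly some residual case mix that the discharge-time variables would have captured; the sensitivity analysis shows both.
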